## *Data Analysis/**Statistical Considerations*

Quantitative data analysis. This longitudinal study design will use random effects (multilevel) models, which account for both repeated measures of individuals and the fact that in one arm individuals are clustered within CBOs. These models allow for outcomes to be missing under the MAR assumption (data is missing at random conditional on the observed outcomes and covariates),^89–91^ which we expect will be adequate. If there is a substantial amount of missing data for covariates or evidence that a more inclusive imputation model should be used, then we will use multilevel multiple imputation implemented via MITML package.^92^ Model assumptions will be evaluated using the comparison group for each analysis, and any modification to the analyses to address violations will be made before final analyses using only comparison group data.

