This study is specifically designed to be sensitive to the changing impacts of the pandemic and the effectiveness of the multilevel interventions in reducing those. Thus, we propose 5 data collection points, every 8 months over 32 months. Our primary outcomes – psychological distress, daily stressors, and economic precarity – tend to be moderately stable^93–98^ but may also be impacted by shocks such as losing a job or getting COVID-19. Given the unknown trajectory of the pandemic and the path of economic recovery, we do not know a priori what the best approach to use for the longitudinal data will be. Therefore, our proposal is to use those in the random comparison sample in order to explore longitudinal models which will capture a large portion of the variability in outcomes over time while also maximizing power to find treatment effects. For example, modeling effects on mean levels of the outcomes post baseline would involve only 1 model parameter but would miss much of the nuance in the data. The comparison respondents will allow us to examine possible alternatives (linear change, piecewise change, adjustments for time-varying events including unemployment and COVID infections) in data without treatment effects. We will conduct analyses and publish a paper which examines fit of alternative longitudinal models to the data, and we will conduct additional power analyses before choosing the approach which best balances model fit and power. For the remainder of the data analysis section, we assume a relatively simple model with an intercept and linear change, while power analyses assume a simple pre-post design which will result in conservative estimates of power.

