**Aim 2**. Test the effects of engagement with CBOs to reduce adverse consequences of the COVID-19 pandemic. Analyses will use both the CBO sample and the random sample of Latinx respondents from across the state. The primary predictor is whether the participant is recruited through the CBO or random community sample. Our analyses test whether respondents recruited from CBOs differ from those in the random sample in outcomes and whether those differences change over time. While the comparison sample is a random probability sample of Latinx immigrants, the CBO sample consists of respondents already connected to a CBO, thus we propose to use propensity score matching^101,102^ with data collected at baseline to match those in each sample. The matched samples used for data analysis will adjust for systematic differences between the random sample and those who engage with CBOs. Our baseline measures have been chosen to include variables which are likely to predict an individual’s exposure to a CBO. To examine the effects of engagement with CBOs, we propose a longitudinal model with random effects for both individuals and CBOs. The model will also adjust for effects of the RIWP intervention observed in Aim 1. We note that the adjustment for clustering within CBOs only takes place for those in the CBO arm; in the comparison arm where there is no nesting, these random effects are assumed to be zero.^103,104^ In mixed notation the model for psychological distress is:

${Distress}_{tij}= B_{000}+{\gamma_{001}\left( CBO \right)+{B_{100}\left( Time \right)+\gamma_{101}\left( CBO*Time \right)\boldsymbol{+B}}_{\boldsymbol{010}}\left( \boldsymbol{covariates} \right)+{B_{020}\left( RIWP \right)+B_{030}\left( RIWP*Time \right)+ u_{00j}+u}_{10j}\left( Time \right)+r_{0ij}+r_{1ij}(Time)+ e}_{tij}$

where CBO is an indicator indicating whether individual *i* is engaged with the CBO, Time is a variable indicating the time of observation in years. For this analysis, Time will be centered around the midpoint of the study because engagement with the CBO is ongoing from before the study began. Thus, our aim is answered by Y_001_ which is the difference in mean levels of distress, adjusted for covariates, between those who experience the CBO and those in the random sample and by Y_101_ which is the difference in slopes over time between those who experience the CBO and those in the random sample.

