**Aim 3.** Test the effects of RIWP and engagement with CBOs to increase access to benefits of structural interventions (local/state relief-related policies). For this aim, the outcome will be a binary indicator for whether each participant accessed the structural interventions which are implemented. The analyses will be similar to Aim 2, but will use a logit link and consequently drop the e_tij_ term. As mentioned above, while this is written to assume linear changes, we have proposed a process for selecting the longitudinal model to be used with data from the comparison sample and using statistical simulations to evaluate power of the different alternatives.

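### The time form is chosen on the random sample, which is also the comparator in Aims 2 and 3, so the CBO-by-time test can reject somewhat too often; Aim 1 is unaffected

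*Protocol*

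**What the plan says.** All the text is in the Protocol, Data Analysis/Statistical Considerations.

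- **Choosing the form.** Because the course of the pandemic is unknown, "our proposal is to use those in the random comparison sample in order to explore longitudinal models". The candidates are "possible alternatives (linear change, piecewise change, adjustments for time-varying events including unemployment and COVID infections) in data without treatment effects". A single post-baseline mean is also mentioned, as an example that would miss nuance. The only rule given is "choosing the approach which best balances model fit and power", after further power analyses.
- **Assumption checks.** The opening paragraph has assumptions checked in whichever group serves as comparator. It adds that "any modification to the analyses to address violations will be made before final analyses using only comparison group data".
- **Aim 1.** Only CBO participants are analysed.
- **Aim 2.** "Analyses will use both the CBO sample and the random sample of Latinx respondents from across the state". To align the two groups, "we propose to use propensity score matching"; no ratio is given. The aim is answered by a mean-level contrast (gamma_001) and by gamma_101, which is "the difference in slopes over time between those who experience the CBO and those in the random sample".
- **Aim 3.** The analysis follows Aim 2 with a logit link, and "we have proposed a process for selecting the longitudinal model to be used with data from the comparison sample".

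No part of the random sample is held out, and no allowance for the selection is described.

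**The concern.** A group without a treatment effect is not the same as a group independent of the test. Among several time forms, the one that fits the random sample best tends to be the one along which that sample's observed change is large, partly by chance. If the same observations are then set against the CBO group, which does not share that chance variation, the difference along the chosen form is biased away from zero in absolute size.

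What is at stake is the error rate of the CBO-by-time test: gamma_101, or its piecewise version if that form is chosen. A spurious difference in slope would be read as an effect of CBO engagement. The same applies to modifications made after assumption checks on comparison-group data. The Protocol's null check does not cover this. It is reported for Aim 2 only and uses ANCOVA data in a pre/post design, where no form is chosen.

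**Working it through.** **Inputs from the Protocol.** Random sample 1000 with 30% attrition, so 700 completers. CBO sample 300 with 10% attrition, so 270 completers, about 135 of them TAU. Five waves, over-time correlation .68, ICC .03 within CBO, five CBOs, effect size .30.

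**Assumptions of mine.** Two-sided .05 (no alpha is stated); AIC or BIC as the selection rule; complete data at the retained sizes; known covariance (compound symmetry or random slopes); no adjustment for time-varying events.

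**1. The plan's own power figures.** Residual SD = sqrt(1 − .68²) = .733.

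- Aim 1, 135 per arm: SE = .733 × sqrt(2/135) = .0892; .30/.0892 − 1.96 = 1.40; power .919, against .91 stated.
- Aim 2, 270 versus 700, between-CBO variance spread over 5 CBOs: SE² = .538 × (1/270 + 1/700) + v/5. With v = .03 × .538, power is about .97. With v = .03, it is about .89. The stated .92 lies between.

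These figures are not in dispute. They come from a pre/post design and say nothing about the selection step. The Protocol states no type I error figure to reproduce.

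**2. How much random-sample noise enters the contrast.** Share = (1/n_RS) / (1/n_RS + 1/n_CBO).

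- 700 versus 270: 28%.
- 700 versus 135: 16%. This is the relevant case when RIWP and RIWP-by-time are in the model, because gamma_101 then compares TAU with the random sample.
- 135 TAU with ICC .03: 27 per CBO, design effect 1 + 26 × .03 = 1.78, effective size 135/1.78 = 76, share about 10%.

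The smaller the share, the less the selection can distort the test.

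**3. Simulation under the null.** Both groups follow the same true trajectory. The form (post-baseline step, linear, piecewise, quadratic) is chosen in the random sample, and all CBO-by-form terms are tested jointly at .05.

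| Setting | AIC | BIC |
|---|---|---|
| 700 v 270, no clustering, flat trajectory | .073–.076 | .065–.067 |
| same, linear trend of .05 per wave | .067–.068 | .053–.055 |
| same, drop then flat | .058–.059 | .052–.053 |
| same, clearly curved | about .050 | about .050 |
| chosen on 700, tested on 270 matched, flat | .067 | .061–.063 |
| 700 v about 135 TAU, RIWP adjusted, ICC .03, all trajectories | .049–.058 | .050–.056 |
| chosen and tested on the same 270 matched, no clustering | up to .093 | not given |

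With a different set of candidate forms, the 700 v 270 range is .051–.072 (AIC) and .052–.064 (BIC). Keeping all 270 CBO completers with ICC .03 (design effect 1 + 53 × .03 = 2.59, effective size about 104) gives .049–.062 over both rules.

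**4. Controls.** A form fixed in advance gives .049–.051. A form chosen in random-sample members outside the test (350/350 or 430/270) gives .049–.051. The Aim 1 analogue gives .050. The excess appears only when the selection data are also a compared arm.

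**The case against.** Choosing the form without looking at CBO outcomes is a deliberate safeguard, and it is better than choosing after seeing the group difference. The Protocol also commits to further power simulations before the choice, and the final form may be settled in the SAP. Pandemic outcomes may well have a marked shape, in which case the error rate is essentially nominal. All of this stands, and it limits the size of the problem. It does not make the stated rule right for Aims 2 and 3.

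A reader might infer more than the documents support:

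- **That the test always rejects too often.** It does not. The rate depends on the trajectory, the selection rule and the analysis set.
- **That error rates of .08 to .10 follow.** Such figures arise at 700 v 270 if a significant result on either of two piecewise coefficients counts as success. That rule alone rejects at .090 with a fixed knot and no selection, and the Protocol states no such rule. Figures that omit the CBO random effects and the RIWP terms also overstate the result under the Aim 2 model as written.
- **That a known inflation applies to Aim 3 or to gamma_001.** The mechanism carries over to CBO-by-time terms in Aim 3, but no size has been shown for the logit model or for the mean-level contrast.
- **That the plan claims the selection is free of cost.** It makes no such claim; it simply describes no allowance for it.

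**Conclusion.** The point holds in a limited form. The random sample both selects the time form and serves as comparator in Aims 2 and 3, with no stated separation, so the selection is independent of the test only in Aim 1. Under assumed AIC or BIC selection and a joint test, the CBO-by-time test runs at about .05 to .07 without CBO clustering and at about .05 to .06 under the Aim 2 model with RIWP adjustment and ICC .03. The latter assumes that CBO-level variance follows the same over-time correlation as the individual-level outcome. The worst case examined is about .09, when the same 270 matched respondents are used for both steps without clustering. The excess is largest for a nearly flat trajectory, which is plausible given that the Protocol calls the outcomes moderately stable. This is a minor correction that is worth making because it is cheap.

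**What to change.** Keep the random-sample exploration for Aim 1. For Aims 2 and 3, adopt one of the following:

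1. Prespecify a single CBO-by-time contrast, for example wave as categorical with one fixed contrast, so that nothing is selected.
2. Choose the form only in random-sample members outside the matched analysis set, provided the matching ratio leaves enough of them. One-to-one matching of completers would leave 700 − 270 = 430. Matching at enrolment would leave 1000 − 300 = 700, or about 490 after 30% attrition.

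Apply the same rule to model modifications made on comparison-group data.

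The cost is wording in the Protocol or SAP. Under option 2 the exploration set is smaller and less like CBO users, since unmatched respondents are those who resemble them least, so the chosen form may suit the matched set less well. Under option 1 the fixed contrast may fit less closely and lose some power. Neither option removes anyone from the Aim 2 or Aim 3 tests.

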| Psychological Distress | 1. DSM Level 1 Cross-Cutting Symptom Measure Adult^72^  2. COVID-19 & MH Impacts^73^ | - Broad Psychopathology measure; 13 psychiatric domains  - Emotional health, worries | - 23 items; 2-week timeframe; reliable & valid; clinically useful, PhenX  -13 items; PhenX |
| Daily Stressors | 1. Perceived Stress Scale^74^  2. Effects of COVID-19 Outbreak^75^ | - Current stressors  - Stressful effects & behaviors | - 10 items; reliable & valid; PhenX  - 11 items; PhenX |
| Economic Precarity | 1. Job Insecurity - General Social Survey 2018^75^  2. RAND American Life Panel Impacts of COVID-19 Survey | - Measures likelihood of losing job and obtaining another job  - COVID-19 Related Household Finances | - 2 items; PhenX  - 6 items; PhenX |
| Access to Resources | Satisfaction with Resources Scale^76^ | - Assesses access to resources in 12 domains | - 12-items; used with newcomers |
| Social Support | Medical Outcomes Study Social Support Survey, 8-item version^77^ | - 2 subscales: instrumental and emotional | - 8 items; reliable & valid; PhenX |
| Cultural Connectedness | Language, Identity and Behavior Acculturation Scale,^78^ short | - Multiple dimensions of cultural connections | - 16 items (parallel versions of 8 items for U.S. culture and home culture) |
| Mental Health and Health Services Use | 1. Composite International Diagnostic Interview (selected questions)^79^  2. Access to Health Services^80^ | - Measures counseling and medications received from a helping professional  - selected items | - 2 items; reliable, valid & used with immigrants  - 2 items on health services use; PhenX |
| Discrimination | Experience of Discrimination (EOD) Scale^81^ | - Measures discrimination in 9 domains | - 9 items; reliable & valid; used with Latinx & Black adults; available in Spanish |

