Random assignment. Randomization of the CBO-recruited sample (n=300) into RIWP or treatment-as-usual waitlist control group (TAU) will occur after completion of timepoint 1 surveys and will be based upon a computerized algorithm that stratifies randomization by CBO site.

RIWP implementation. RIWP will be implemented with 30 participants from each CBO site (n=150) from Months 5-12. RIWP will be integrated into existing activities and services in different ways at each site, with the goal of creating a sustainable intervention and multilevel change. All RWIP activities (Learning Circles and advocacy) will be conducted remotely for now. Once state and UNM COVID restrictions are lifted, some in-person Learning Circles and advocacy meetings may occur. The treatment-as-usual waitlist control group will participate in RIWP after two years (3 timepoints) of data collection, from Months 29-35. RIWP involves a sustainable and replicable partnership model between refugees, CBOs, and universities (see Figure 1 for conceptual model). Newcomer families and undergraduate advocates work together for 16 weeks to: a) increase newcomers’ abilities to navigate their new communities; b) improve newcomers' access to community resources; c) enhance meaningful social roles by valuing newcomers' cultures, experiences, and knowledge; d) reduce newcomers' social isolation; and e) increase community responsiveness to newcomers. RIWP is implemented by university students enrolled in a 2-semester course, and has two elements: 1) Learning Circles, which involve cultural exchange and one-on-one learning opportunities; and 2) Advocacy, which involve collaborative efforts to mobilize community resources related to health, housing, employment, education, and legal issues and to create policy/system changes. Meeting in weekly Learning Circles, newcomers and their student partners learn from each other during cultural exchange time designed to facilitate sharing of cultural and intergenerational knowledge and to help newcomers recognize their contributions and potential to effect changes in their communities. During one-on-one learning time, newcomer and student participants practice English, fill out job applications, and engage in other activities newcomers want to pursue to expand knowledge, improve skills, or accomplish goals. RIWP is holistic, multilevel, and strengths-based, and has an explicit social justice orientation that is informed by an ecological perspective. A holistic intervention is essential because it addresses the multiple sources of newcomers’ psychological distress, including psychological (past traumas), material (poverty, lack of access to resources), physical (physical ailments from war, violence and deprivation), social (loss of meaningful social roles and social support), educational (limited English proficiency, literacy), and cultural disconnection from traditional cultural practices). A strengths-based perspective is important because newcomers have survived in the face of tremendous hardships and have numerous strengths on which to build, including cultural knowledge (and often extensive cross-cultural experience), resourcefulness (experience operating in resource scarce situations), effective coping strategies (that have enabled them to survive), multilingual abilities (many arrive already speaking two or more languages), and often strong family and community bonds and support. Newcomers are often pathologized by well-intentioned service providers and systems, rather than recognizing that most are resilient people who have faced abnormally difficult circumstances. Not only is it crucial for newcomers’ mental health and well-being to acknowledge their expertise and build upon their strengths, but also their knowledge and experiences are assets from which other Americans can benefit. Thus, mutual learning is an intentional and core component of RIWP. This emphasis also ensures that RIWP is appropriate for multiple linguistic and cultural groups who can participate simultaneously and learn from one another as well as from longer-term residents of the U.S. Guided by ecological theory, RIWP focuses not only on newcomers adjusting to their new contexts, but also on changing environments when they are inequitable or constraining (e.g., mobilization or redistribution of resources). Ensuring that RIWP creates change at multiple levels is important because newcomers have urgent learning, resource, and health needs that must be addressed at the individual level in order to enable them to work collectively with others to create community and structural changes that address the root causes of mental health disparities and social inequities, which result in sustainable social change.

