**Aim 1.** Test the effects of the RIWP intervention to reduce adverse consequences of the COVID-19 pandemic. The principal objective of this study is to test the efficacy of the RIWP intervention for participants recruited from CBOs. Because only individuals recruited from the CBO sample are eligible to be randomized to receive the RIWP intervention or treatment as usual, analysis for this aim includes only CBO participants. To examine the effects of the RIWP intervention, we propose a linear model with random effects for individuals. As randomization happens within CBO, there is not an explicit random effect for this included, but we do propose to use sandwich estimators,^99,100^ to adjust standard errors for any unexpected impacts of this clustering. In mixed notation the model for psychological distress is:

${Distress}_{ti}= B_{00}+{B_{01}\left( RIWP \right){+B}_{02}\left( Time \right){+B}_{03}\left( Time*RIWP \right){+\boldsymbol{B}}_{\mathbf{0}\boldsymbol{N}}\left( \boldsymbol{covariates} \right)+ r_{0ij}+r_{2ij}(Time)+ e}_{ij}$

where participation in the RIWP plus CBO is indicated by a dummy code for RIWP. Because baseline data is collected before randomization, time is centered at baseline and our aim is answered by B_03_ which is the difference in slopes of levels of distress, adjusted for covariates, between those who experience RWIP+CBO intervention and those in the CBO group.

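### Selecting the longitudinal model on fit and power could bring post-randomization unemployment into the Aim 1 model, so that B_03 is no longer the total RIWP effect

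*Protocol*

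**What the plan says.** All places are in the protocol.

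- **Candidates and rule.** Data Analysis/Statistical Considerations says that the best longitudinal approach is not known in advance. The random sample will be used to examine "possible alternatives (linear change, piecewise change, adjustments for time-varying events including unemployment and COVID infections) in data without treatment effects". The final choice follows further power analyses and means "choosing the approach which best balances model fit and power". No criterion excludes variables that treatment may change.
- **Reason given.** The primary outcomes "may also be impacted by shocks such as losing a job or getting COVID-19".
- **Carry-over.** The linear models shown for the aims are working assumptions. The Aim 3 text repeats that "we have proposed a process for selecting the longitudinal model to be used with data from the comparison sample", and secondary aim (a) reuses the models developed on the random sample.
- **Effect under test.** For Aim 1, "our aim is answered by B_03_ which is the difference in slopes of levels of distress, adjusted for covariates". The covariates are not listed or limited to baseline.
- **Timing.** Under Data Collection Procedures (Random assignment), randomization follows the T1 survey.
- **What RIWP does.** Under RIWP implementation in the same section, participants and students "practice English, fill out job applications, and engage in other activities newcomers want to pursue", and employment is one of the areas that advocacy addresses.
- **Outcome measure.** One of the two economic precarity instruments in Table 1 is described as "Measures likelihood of losing job and obtaining another job".

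**The concern.** Aim 1 asks for the total effect of being randomized to RIWP. A covariate recorded after randomization is safe only if treatment does not change it. Unemployment at T2 to T5 may fail that condition. Some RIWP activities are directed at getting work, and the protocol itself expects job loss to move the primary outcomes. For economic precarity the covariate also overlaps with what is being measured.

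Adjusting for such a variable would leave only the part of the effect that does not pass through employment. Even that part would not be cleanly randomized if unemployment and distress share unmeasured causes.

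Selecting in the random sample protects against choosing a model by its treatment result. It gives no protection here, because that sample contains no RIWP effect and so cannot show that a covariate lies on the RIWP pathway. Both selection criteria can reward such a covariate: it explains outcome variance, and lower residual variance raises calculated power if the effect is held at .30.

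**Working it through.** **1. Reproduce the Aim 1 power.** Inputs from the Power paragraph: effect .30, baseline-posttest correlation .68, CBO attrition 10%. With 150 per arm, 150 × 0.90 = 135 remain. Two-sided alpha .05 is an assumption, because the protocol states none.

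- Residual SD after baseline adjustment: √(1 − 0.68²) = 0.733.
- Standard error: 0.733 × √(2/135) = 0.0892.
- Power: Φ(0.30/0.0892 − 1.96) = 0.919 (0.918 with the noncentral t). The protocol states .91, so the figure reproduces.

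**2. Effect of adjusting for a mediator, by formula.** If a share f of the effect runs through the event, the adjusted contrast is 0.30 × (1 − f). The protocol gives no value for f, so a range is shown with the same standard error.

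| f (assumed) | fitted effect | power |
|---|---|---|
| 0 | 0.30 | 0.919 |
| 10% | 0.27 | 0.857 |
| 20% | 0.24 | 0.767 |
| 30% | 0.21 | 0.653 |
| 50% | 0.15 | 0.390 |

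**3. Simulation check.** There were 4,000 runs with 135 per arm and the total effect fixed at −0.30. ANCOVA was fitted with and without a binary post-randomization event. Event rates and event effects are assumptions. Expected adjusted effect = 0.30 − (difference in event rates) × (event effect), for example 0.30 − 0.10 × 0.6 = 0.24.

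| Event rate, TAU vs RIWP | event effect (SD) | expected size, adjusted | estimate, adjusted | power, baseline only | power, adjusted |
|---|---|---|---|---|---|
| 25% vs 15% | 0.3 | 0.27 | −0.272 | 0.922 | 0.864 |
| 25% vs 15% | 0.6 | 0.24 | −0.240 | 0.925 | 0.812 |
| 30% vs 15% | 0.6 | 0.21 | −0.207 | 0.916 | 0.688 |
| 30% vs 10% | 0.6 | 0.18 | −0.178 | 0.932 | 0.543 |
| 25% vs 25% | 0.6 | 0.30 | −0.300 | 0.919 | 0.947 |

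Power falls slightly less than in step 2 because the event also removes some residual variance. The last row is the key contrast: when treatment does not change the event, the estimate is intact and power rises. A power comparison built on the random sample with the effect held at .30 would see only that gain.

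**4. Limits of the calculation.** It uses the simple pre/post design of the protocol's own power section, whereas B_03 is a difference in slopes. It also assumes no unmeasured common cause of the event and the outcome. It shows direction and scale only.

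**The case against.** The best defence is that nothing has been fixed. The adjustment is one of several alternatives, the models written out for Aims 1 and 2 contain no time-varying event, and a covariate list is commonly left to a statistical analysis plan. All of that is true. What remains is what the protocol does state: it names the candidate and sets a selection rule that has no means of rejecting a mediator.

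A second defence is that job loss and infection are presented as outside shocks, and adjusting for a true shock is harmless and gains precision. The last simulation row confirms this. It holds for events that RIWP does not change, and the protocol's description of RIWP makes that doubtful for unemployment.

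Four stronger readings might be inferred, and the document does not support them:

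- *That RIWP aims to change both events as outcomes.* Neither is a listed outcome. Employment status appears among the demographic, control and moderator variables, and COVID infection is nowhere named as an RIWP target.
- *That the adjusted model will be chosen.* Nothing in the protocol shows which candidate will win.
- *That a particular percentage of the effect will be lost.* Any such figure rests wholly on assumed inputs.
- *That the CBO contrasts in Aims 2 and 3 are harmed in the same way.* CBO engagement predates the study, so even T1 employment follows exposure there. The argument reaches only the RIWP terms in those models.

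**Conclusion.** The concern holds for Aim 1, and for the RIWP terms in the Aim 2 and 3 models, as a risk that the stated selection rule leaves open. The case is well supported for unemployment and strongest for economic precarity. For COVID infection it rests only on timing.

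The size is unknown. It is nil if RIWP does not change the event and grows with the share of the effect that runs through employment. For assumed shares of 10% to 30%, the planned .30 would be fitted as .27 to .21, with power of .86 to .65 by formula, against the stated .91. The change should be made before the model is selected.

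**What to change.** Amend the model-selection paragraph in Data Analysis/Statistical Considerations to state that:

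1. selection in the comparison sample concerns only the form of time and the covariance structure;
2. the confirmatory Aim 1 model, and the RIWP terms in the Aim 2 and 3 models, adjust only for covariates measured at T1;
3. models with time-varying unemployment or COVID infection are reported as sensitivity, mechanism or descriptive analyses. The mediators now named in secondary aim (a) are protective factors, so any mechanism analysis of unemployment should be labelled as an addition.

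This keeps the comparison-sample selection process and costs a sentence or two of text. The price is some forgone reduction in residual variance: in the simulated case where RIWP leaves the event unchanged, power of .919 instead of .947. The T1-only rule does not resolve covariate choice for the CBO contrast, where engagement began before T1.
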